### Monitoring

A data protection officer independent from the researcher will be assigned and monitors 1) the protection of the rights and well-being of the participants; 2) whether the reported research data is accurate and completely verifiable in source documents; and 3) whether the implementation of the research is consistent with the approved protocol/amendment(s) at that time, with GCP and the applicable legal requirements [146]. After including the first five participants, all data will be monitored. That is, the accuracy and completeness of all data (on item/trial level) per participant will be checked. After including participant five to ten, the completeness and accuracy of the data on summary/scale level will be checked for all participants. Thereafter, data on summary/scale level will be checked randomly for one in five participants. Outcomes of this data monitoring will be summarised in an overview and reported to all research personnel.

Based on previous studies on MBI for children and Mindful Parenting, deterioration as a result of family MBI is not expected. Therefore, no interim analysis will be conducted. Adverse events (AEs) are defined as any undesirable experience occurring to a participant during the study, whether or not considered related to the family MBI. All AEs reported spontaneously by the participant or observed by the researcher or mindfulness teachers will be recorded. All serious adverse events (SAEs, resulting in death, life threatening, requiring hospitalisation or other important medical events) will be communicated to the principal and coordinating researchers, who will report the SAEs to the accredited ethics committee that approved the protocol, within fifteen days after the sponsor has first knowledge of the SAE. SAEs that result in death or are life threatening should be reported expedited. The expedited reporting will occur not later than seven days after the responsible researcher has first knowledge of the SAE.

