MYmind consists of eight weekly 90-min group sessions for children (groups of approximately 5–8), and parallel group sessions for their parents of equal length and duration. The child and parent sessions take place in separate rooms, with the exception of sessions 1, 5 and 8, where part of the session is together in the same room. In the sessions (playful) mindfulness exercises are done and education is given around the following themes, one per session: 1) Beginners’ mind, 2) Home in our body, 3) The breath, 4) Distractors!, 5) Stress, 6) High way, walking way, 7) Acceptance & autonomy, and 8) The future. Both children and parents receive daily homework during the eight weeks of training (15 min for child and 30–45 min for parent, 6 days/week). Theory and exercises are described in a workbook that both children and parents receive together with audio-files to guide the mindfulness exercises. As children with ADHD may have motivational problems, a reward system is incorporated in the course for the children to enhance motivation to practice in the sessions and at home. The 8-week course is followed by eight weeks of home self-practice, and a single joint child-parent 90-min booster session. In the booster session, participants share experiences of the mindfulness practice in the last eight weeks where they did not have the support of the group training, rehearse certain practices in order to remind the families of the possible joys and benefits of mindfulness practice, and are encouraged to think about how to implement mindfulness in their lives and to renew their intentions. Participants who attend four or more sessions will be considered as ‘completers’.

The first trial on an MBI for children combined with Mindful Parenting was conducted by Bögels et al. (2008) [64], which resulted in the MYmind training. Since then, several non-randomised pilot studies have been conducted with the MYmind training in child and adolescent samples with ADHD [54, 55, 65–67] and with ASD [68, 69]. Findings are promising and show that the MYmind training is feasible and acceptable [70].

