#### CAU

According to the Dutch Multidisciplinary guidelines for the diagnosis and treatment of ADHD [76], CAU for children aged 8–16 years consists of psycho-education and the prescription of medication approved for ADHD and/or evidence-based parent and/or teacher-administered behaviour therapy, preferably both medication and behaviour therapy. First-line option for medication is a psychostimulant, second-line options are atomoxetine or alpha-2 presynaptic agonists. Participants in the CAU-group will be informed that it is not allowed to participate in a mindfulness programme until the 2-month follow-up assessments of the study.

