Assessments will take place at baseline (T0), end of treatment (T1), two (T2) and six (T3) months after end of treatment. For the family MBI condition, T0 will be scheduled in the two weeks prior to the start of the intervention and T1 in the two weeks after the 8th session of the MYmind training. The booster session will be followed by the first follow-up assessments (T2) which will be two months after T1 and the second follow-up assessments (T3) will be scheduled half a year after T1. Intervals between assessments will be kept similar for the family MBI and CAU condition. For baseline, end of treatment and 6-month follow-up assessments, participants will be invited to a location of Karakter. Assessments will be conducted by a researcher or research assistant. Participants will be asked to interrupt ADHD medication intake 48 h prior to these assessments. For the 2-month follow-up assessments, both parent and child will receive an invitation to complete questionnaires online (not at Karakter). School teachers will be asked to complete all questionnaires online at baseline, end of treatment and 2-month follow-up. See Table 1 for which assessments for children will be taken at which time points and Table 2 for assessments for parents and time points. Further, see Fig. 1 for a flowchart on recruitment and the study procedure.

**Table 1 Tab1:** Assessments for children and time points

Assessments for children	Time points			
*Descriptives*				
Demographics	T0			
WISC-III (Vocabulary and Block Design)	T0			
Investigator-rated K-SADS-PL	T0			
Self-rated PDS	T0			T3
*Primary outcome measure*				
*Parent-rated child self-control*				
BRIEF-P	T0	T1	T2	T3
*Secondary outcome measures*				
*Teacher-rated self-control*				
BRIEF-T	T0	T1	T2	
*Computerised tasks of self-control*	T0	T1		T3
*Psychological symptoms*				
Parent-rated CPRS-L:R (subscales DSM-IV inattentive symptoms, DSM-IV hyperactivity-impulsive symptoms, oppositional, anxious-shy, social problems, emotional lability index)	T0	T1	T2	T3
Teacher-rated CTRS-L:R (subscales DSM-IV inattentive symptoms, DSM-IV hyperactivity-impulsive symptoms, oppositional, anxious-shy, social problems, emotional lability index)	T0	T1	T2	
Parent-rated SRS	T0	T1		T3
Teacher-rated SRS	T0	T1		
Self-rated RRS (Brooding)	T0	T1		T3
*Well-being*				
Parent-rated KIDSCREEN-11	T0	T1		T3
*Mindfulness*				
Self-rated CAMM	T0	T1	T2	T3
*Tertiary measures*				
*Self-rated*				
BEQC	T0	T1		T3
HSCP	T0			
ICU (ages 11+)	T0	T1		

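### Adverse events are captured passively, and one of the capture channels exists only in the MBI arm, so AE counts by arm would not be comparable

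*Protocol article*

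**What the plan says.** All references are to the protocol article.

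- **Definition (Monitoring).** An AE is "any undesirable experience occurring to a participant during the study, whether or not considered related to the family MBI". It therefore applies to both arms.
- **Capture (Monitoring).** "All AEs reported spontaneously by the participant or observed by the researcher or mindfulness teachers will be recorded". This names three channels: spontaneous report, the researcher and the mindfulness teachers. Tables 1 and 2 list no AE item.
- **Expectation (Monitoring).** The article says that "deterioration as a result of family MBI is not expected" and gives this as the reason for having no interim analysis.
- **MBI contact (Family MBI).** "MYmind consists of eight weekly 90-min group sessions for children (groups of approximately 5–8), and parallel group sessions for their parents", followed after eight weeks of home practice by "a single joint child-parent 90-min booster session".
- **CAU contact (CAU).** Control families are told that "it is not allowed to participate in a mindfulness programme until the 2-month follow-up assessments of the study". They have no mindfulness teacher within the trial.
- **Researcher contact (Procedure and treatment allocation).** Both arms attend on site at T0, T1 and T3, at similar intervals. T2 is completed online.
- **Reporting (Statistical analyses).** Results are to follow CONSORT.

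**The concern.** The definition is symmetric between arms but the means of detection is not. One of the three channels is present in one arm only, and it is the channel with the most frequent contact. The imbalance is greatest between T0 and T1, while the course is running.

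If AE counts are shown by arm, which CONSORT reporting makes likely, an excess with MBI could come from more observation rather than more harm. Similar counts would not reassure either, because passive capture misses events in both arms. An analysis plan cannot repair this later, since events that nobody asked about cannot be recovered.

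**Working it through.** The article gives no figure for AEs, so there is none to reproduce. The check counts contacts and then works through an illustration with assumed rates.

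**Step 1. Scheduled face-to-face contacts after baseline with a named observer**

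| Contact | MBI | CAU |
|---|---|---|
| Weekly sessions | 8 | 0 |
| Booster | 1 | 0 |
| T1 on site | 1 | 1 |
| T3 on site | 1 | 1 |
| **Total** | **11** | **2** |

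From T0 to T1 the count is 8 + 1 = 9 against 1. The MBI total is a maximum: a family that attends four sessions in all, the article's threshold for a completer, has 4 + 2 = 6 against 2. Ordinary clinic visits do not redress the balance, because both arms continue CAU and treating clinicians are not a named AE source.

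**Step 2. Effect on recorded events at equal true risk (assumed rates, not in the document)**

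Let p be the true risk in both arms. Let s be the share of events captured by spontaneous report or by the researcher, taken as equal in both arms. Let t be the share of the remaining events that a teacher picks up.

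- CAU recorded = p × s
- MBI recorded = p × [s + (1 − s) × t]
- Ratio = 1 + t × (1 − s)/s, so p cancels

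| s | t | Ratio MBI:CAU |
|---|---|---|
| 0.7 | 0.1 | 1 + 0.1 × 0.3/0.7 = 1.04 |
| 0.5 | 0.3 | 1 + 0.3 × 0.5/0.5 = 1.30 |
| 0.3 | 0.5 | 1 + 0.5 × 0.7/0.3 = 2.17 |

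Example with 50 per arm, p = 0.20, s = 0.5 and t = 0.3:

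- True events: 0.20 × 50 = 10 in each arm
- CAU recorded: 10 × 0.5 = 5.0
- MBI recorded: 10 × (0.5 + 0.5 × 0.3) = 6.5

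Both arms fall short of 10, and CAU falls shorter.

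**Step 3. With the same enquiry in both arms**

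If only solicited events enter the comparison, the teacher channel drops out (t = 0) and the ratio at equal true risk is 1.00.

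**The case against.** Much of the case on the other side stands.

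- **Deterioration is measured in both arms.** A reader might infer that the expectation of no deterioration cannot be tested at all. The document does not support that. Parent-rated BRIEF and CPRS are collected at all four time points. Teacher ratings, KIDSCREEN, child brooding, DASS-21, WHO-5 and MHC-SF follow the same schedule in both arms. Average worsening can be compared on these. They do not record discrete events with date and severity, and the article does not name them as AE sources.
- **Healthcare use is asked about in both arms.** The TiC-P covers the child at T1, T2 and T3 and the parent at T3. Medication and reasons for discontinuation are also recorded. This may reveal hospital admissions, but Monitoring does not link it to AE or SAE recording.
- **MBI events would not be overstated in absolute terms.** A reader might infer that they would be. Passive capture tends to miss events in both arms; the excess with MBI is only relative to CAU. The expected bias makes MBI look less safe than CAU and does not hide an MBI harm.
- **The contact ratio is not a bias ratio.** It is tempting to give each contact a fixed chance of bringing up an event. At an assumed 5%, 1 − 0.95^11 = 43% against 1 − 0.95^2 = 10%. That ignores spontaneous reports outside visits, incomplete attendance, and recall: a weekly session covers about a week, while T1 covers about eleven. It also treats a group session as equal to an individual assessment. Those figures should not be used.
- **This is a condensed article.** A fuller protocol may contain an AE form, and the article plans no formal between-arm AE test. But it does state a capture rule, and that rule, followed as written, is unequal between arms.

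**Conclusion.** The concern holds in a limited form. The document establishes unequal opportunity to record AEs: up to 11 scheduled face-to-face contacts against 2 after baseline, with one named channel absent from CAU. The expected consequence is under-recording in both arms, less so with MBI, which makes AE counts by arm non-comparable.

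The direction assumes that spontaneous and researcher capture work equally well in both arms. The size cannot be derived from the document; the range of 1.04 to 2.17 only illustrates s from 0.3 to 0.7 and t from 0.1 to 0.5. The primary and secondary efficacy analyses and the sample size are not affected. The change is worth making because participants are children and the remedy is cheap.

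**What to change.** - Add the same short AE question to the T1, T2 and T3 questionnaires for parent and child in both arms: new or worsened problems, date and severity, with the same wording and recall period.
- Use TiC-P responses in both arms as a prompt to check for possible SAEs.
- Log the source of each AE (solicited, spontaneous, researcher or teacher).
- Base the between-arm AE summary on solicited events only, and list teacher-observed events separately.

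The cost is a few items in the existing electronic forms and a line in the protocol, slightly longer questionnaires, and more recorded AEs. No extra visit is needed. The change equalises the opportunity to report; it does not remove any influence of families knowing their allocation.

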## Discussion

Self-control is a malleable determinant of success in health, wealth, parenting, and avoiding crime [147]. Hence, improving self-control in children with self-control deficits has an important impact on their life and society. An example of a clinical population in which targeting self-control in treatment is pressing is youth with ADHD. ADHD is associated with adverse outcomes including impediment on academic achievement, mental and substance use disorders, criminality, and employment [148]. Current CAU for youth with ADHD is often not sufficient in improving self-control. Furthermore, CAU is generally not focused on mental health and well-being of the parents, although this has impact on the (treatment of the) child as well. ADHD medication can have undesired side effects, is refused by some families, compliance may be low, and improvements do not last after medication discontinuation [35]. These shortcomings might be addressed by offering a family-based MBI in addition to CAU. Self-regulation is present at the basis of MBIs and work by cognitive neuroscientists demonstrates that brain structures and functions that are involved in self-control are altered with (mindfulness) meditation. There is strong evidence of positive overall effects of MBIs in children as well as adults [21, 149, 150]. However, studies investigating the effects of MBIs on self-control in youth with ADHD and/or their parents are scarce and there is a need for methodologically stronger trials.

This protocol describes an adequately powered RCT studying family MBI as an innovative non-pharmacological approach in the treatment of youth with ADHD. Children with comorbidities (e.g. ASD, ODD, dyslexia) will be included which has the advantage of increasing the representativeness of the sample for the clinical ADHD population. Where previous studies were uncontrolled or waitlist controlled, the current trial allows comparison with a CAU control group. Actually received CAU prior to and during study participation will be registered in both the control and intervention condition. The intervention is a manualised family MBI (MYmind) for children and their parents given by well trained experienced mindfulness teachers who will be evaluated in terms of both their adherence to the protocol and competence. Another strength of the study is that assessments will be done with different informants allowing taking account of rater effects. Questionnaires will not only be rated by self and parents, but also by teachers who are not involved in the intervention. Next to subjective ecologically valid questionnaires, objective computerised tasks will be administered to explore effects on different aspects of self-control. Further, a broad range of outcomes (e.g. neuropsychological functions, clinical symptoms, positive health) will be assessed in both the child and the parent. This not only allows studying the effect of family MBI on child and parental outcomes but also how they relate to each other. This will increase our understanding of the influence of parental symptoms, functioning and well-being on the child and vice versa, and the possible role that MBI on a family level may play in targeting child and/or parental needs. In addition, follow-up assessments until six months after the end of treatment make it possible to investigate both the short- and long-term effectiveness of the intervention. In a similar trial of an MBI in adults with ADHD, significant effects on self-control assessed with the BRIEF were only found at follow-up [58], as it might take more time and practice before MBI results in improvement of real-life self-control skills. Effects of self-control are suggested to follow a continuum, therefore interventions that achieve even small improvements in self-control for individuals, could shift outcomes across the population as a whole in a positive direction to impact health, wealth and crime rates [1]. Finally, ADHD is one of several psychopathologies (e.g. ODD, CD, addictions, mood- and anxiety disorders) that involve self-control deficits. Hence, results of the proposed RCT are in a cross-disorder perspective informative for a broad clinical population.

## Abbreviations

ADHD: Attention Deficit/Hyperactivity Disorder
AE: Adverse Event
AQ-10: Short Autism Spectrum Quotient
ASD: Autism Spectrum Disorder
BEQC: Body Experience Questionnaire for Children
BRIEF: Behaviour Rating Inventory of Executive Function
CAMM: Child and Adolescent Mindfulness Measure
CAU: Care-As-Usual
CD: Conduct Disorder
CEQ: Credibility/Expectancy Questionnaire
CMO: Central committee on research involving human subjects
CPRS-R:L: Conners’ Parent Rating Scales-Revised: Long
CTRS-R:L: Conners’ Teacher Rating Scales-Revised: Long
DASS-21: Depression Anxiety Stress Scale
DSM-5: Diagnostic and Statistical Manual of Mental Disorders, Fifth Edition
DSM-IV: Diagnostic and Statistical Manual of Mental Disorders, Fourth Edition
GCP: Good Clinical Practice
HSCS: Highly Sensitive Child Scale
HSPS: Highly Sensitive Person Scale
ICU: Inventory of Callous-Unemotional traits
IM-P: Interpersonal Mindfulness in Parenting scale
IQ: Intelligence Quotient
K10: Kessler Psychological Distress Scale
K-SADS-PL: Schedule for Affective Disorders and Schizophrenia for School-Age Children-Present and Lifetime Version
MBCT: Mindfulness-Based Cognitive Therapy
MBI: Mindfulness-Based Intervention
MBSR: Mindfulness-Based Stress Reduction
MHC-SF: Mental Health Continuum-Short Form
MINI: Mini-International Neuropsychiatric Interview
ODD: Oppositional Defiant Disorder
PDS: Pubertal/Physical Development Scale
RCT: Randomised Controlled Trial
RRS: Ruminative Response Scale
SAE: Serious Adverse Event
SPIRIT: Standard Protocol Items: Recommendations for Interventional Trials
SRS: Social Responsiveness Scale
SSRT: Stop Signal Reaction Time
SWAN: Strengths and Weakness of ADHD Symptoms and Normal Behaviour
TAC: Teaching Assessment Criteria
TiC-P: Trimbos and iMTA questionnaire on Costs associated Psychiatric illness
VMBN: Association of mindfulness-based teachers in the Netherlands and Flanders
WAIS-III: Wechsler Adult Intelligence Scale-Third Edition
WHO-5: World Health Organization-Five Well-being Index
WISC-III: Wechsler Intelligence Scale for Children-Third Edition
